##### Social and societal functioning

2.3.2.3

The Global Assessment of functioning (GAF) is a clinician-rated scale ranging from 0 to 100 that evaluates psychosocial, occupational, and social functioning. Higher scores indicate better overall functioning, whereas lower scores reflect more severe impairment. The GAF provides a standardized assessment of how symptoms affect an individual’s daily life. The scale has demonstrated adequate reliability and validity (51).

The AMBIT Integrative Measure (AIM, paper version or interactive version) (52) is based on the Hampstead Child Adaptation Measure (HCAM) and the Functional Assessment of Care Environments (FACE) (52), and evaluates outcomes based on changes in areas most relevant to the individual, rather than solely relying on diagnostic outcomes. Its aim is to capture meaningful improvements in daily life, social relationships, and overall psychosocial functioning as experienced by the individual. The measure consists of 43 items across 8 domains of functioning: Daily life, Socio-economic factors, Family relationships, Social relationships, Mental states, Response to situation, Complexity, Power and Control. Items are rated on a 5-point scale ranging from 0 (*no problem*) to 4 (*severe problem)*, with reductions in scores indicating improvement. The AIM is designed to be low-burden and practical for routine use, completed both by the practitioner (case manager in the FACT team or key worker in the AMBIT team) and by a blinded rater. The measure demonstrates good reliability and validity (52).

##### Mentalizing capacity

2.3.2.4

The Reflective Functioning Questionnaire (RFQ) (53) is an 8-item self-report measure of mentalizing that captures an individual’s perceived capacity to understand their own and others’ mental states. It includes two subscales: Certainty (hypermentalizing) and Uncertainty (hypomentalizing). Items are rated on a 7-point Likert scale ranging from 1 (*strongly disagree)* to 7 (*strongly agree*). Higher scores represent hypo-mentalizing whereas lower scores represent more optimal mentalizing. The measure shows good reliability and validity (53).

##### Epistemic mistrust

2.3.2.5

The Questionnaire Epistemic Trust (QET) (54) is a 24-item self-report questionnaire designed to assess epistemic (mis)trust in interpersonal contexts. It consists of 4 subscales: 1) Hypervigilance, 2) Curiosity/Openness, 3) Expectations of Help, 4) Openness to help. Items are rated on a 5-point Likert scale varying from 1 (*totally agree*) to 5 (*totally disagree*). Total scores range from 24 to 120, with higher scores indicating greater epistemic mistrust. The subscales have good to excellent internal consistency and an excellent internal consistency for the total 24-item scale (Cronbach’s alpha α = 0.91). The QET has shown relevant associations with related constructs like personality functioning, symptom distress and quality of life (54).

##### Childhood trauma and attachment security

2.3.2.6

Childhood trauma and adversity will be assessed using the Childhood Trauma Questionnaire (CTQ) (51, 55–57), and the Youth and Childhood Adversity Scale (YCAS) (58). The CTQ is a 28-item self-report measure assessing severity of childhood abuse and neglect, and includes five subscales: 1) Emotional Abuse, 2) Physical Abuse, 3) Sexual Abuse, 4) Emotional Neglect, and 5) Physical Neglect. Items are rated on a 5-point Likert scale, ranging from 1 (*never true*) to 5 (*very often true*), with higher scores indicating greater severity. The questionnaire includes a minimization/denial scale to identify potential under-reporting of trauma, enhancing measurement accuracy and reliability. The CTQ demonstrates good reliability and validity across (clinical) populations (57).

The YCAS is a 13-item retrospective self-report questionnaire assessing exposure to adverse life events (e.g., serious illness, serious parental illness, or “other” adversity). Participants need to indicate whether they have experienced each type of adversity (yes/no). For any endorsed event, participants need to rate the perceived severity on a 7-point scale from 1 (*not at all traumatic*) to 7 (*extremely traumatic*). The YCAS has good reliability and validity (58).

Autonomy and attachment will be assessed using the Autonomy-Connectedness Scale (ACS-30) in Dutch (59, 60). The ACS-30 consists of 30 items across 3 subscales: 1) Self-awareness (awareness of one’s own opinions, desires, and needs during social interactions), 2) Sensitivity to others (empathy and consideration of others’ opinions), 3) Ability to handle new situations (comfort with unfamiliar situations, flexibility, and exploration). Items are rated on a 5-point Likert scale from 1 (*strongly disagree*) to 5 (*strongly agree*), with higher scores indicating greater autonomy and secure attachment. The measure demonstrates good reliability and validity (59).

##### Suicidality

2.3.2.7

The Columbia-Suicide Severity Rating Scale (C-SSRS) (61) is an instrument that screens for suicidal ideation and behavior across four domains: 1) severity of ideation (5 items), 2) intensity of ideation (5 items), 3) suicidal behavior (5 items), and 4) lethality subscale (1 or 3 item(s)). Severity of suicidal ideation is rated on a 5-point ordinal scale: 1= wish to be dead, 2 = nonspecific active suicidal thoughts, 3 = suicidal thoughts with methods, 4 = suicidal intent, and 5 = suicidal intent with plan, with higher scores indicating more severe ideation. Intensity of ideation is rated on a 5-point ordinal scale assessing frequency, duration, controllability, deterrents, and associated distress, with higher scores indicating greater intensity. Suicidal behavior is rated on a nominal scale including actual, aborted, and interrupted attempts; preparatory behavior; and nonsuicidal self-injurious behavior. Lethality is rated on a 6-point ordinal scale for actual lethality, or a 3-point scale for potential lethality if actual lethality is zero. The C-SSRS demonstrates good reliability and validity (61, 62).

The SUICIdal DIfferentiation (SUICIDI) version 3.2 (63) is a clinician-rated instrument designed to differentiate types of suicidality based on the four-type model of entrapment (4ME) (63–65). The SUICIDI assesses four subtypes: 1) Perceptual Disintegration (PD), 2) Primary Depressive Cognition (PDC), 3) Psychosocial Turmoil (PT), and 4) Inadequate Coping or Communication (IC). A total of four points is distributed across these subtypes, reflecting the relative prominence of each in the patients’ presentation. Higher scores within a subtype indicate stronger alignment with that specific pattern of suicidality. Scores can be divided among subtypes when uncertainty exists, but the rater must determine one dominant subtype based on overall clinical impression. The instrument is completed by a trained clinician or caseworker following a structured interview or case review. The SUICIDI demonstrates good to excellent interrater agreement (63).

##### Cost-effectiveness

2.3.2.8

Health-related quality of life will be assessed using the Dutch version of the EQ-5D-5L (66). The EQ-5D-5L is a self-report measure that evaluates health across five dimensions: mobility, self-care, usual activities, pain/discomfort, and anxiety/depression. Each dimension is rated on a 5-point scale ranging from 1 (*no problems*) to 5 (*extreme problems/unable to*), generating a health state that can be converted into a utility score (67). The Dutch tariff (68), will be used to derive utility values from EQ-5D-5L responses, from which quality-of-life adjusted life years (QALYs) will be calculated over the 3 years follow-up period. One QALY represents a year lived in a state of perfect health, combining both quality and length of life into a single metric. Symptom reduction and improvements in daily functioning are expected to increase QALYs, resulting in a dominant incremental cost-utility ratio (greater QALY health gains for lower healthcare costs and non-healthcare costs). These findings would support AMBIT as a more cost-effective treatment compared with treatment as usual (i.e., FACT) (69).

Individual capability will be assessed using the Dutch version of the ICECAP-A (70–72). The ICECAP-A measures five capabilities relevant to quality of life: stability, attachment, autonomy, achievement, and enjoyment. Each of five items is rated on a 4-point Likert scale ranging from 1 (not able to experience capability at all) to 4 (fully able to experience capability). Responses will be transformed into a capability index score using a tariff based on the Dutch general population. Index scores range from 0 (no capability) to 1 (full capability). The ICECAP-A demonstrates good test-retest reliability (ICC = 0.79) and construct validity in a large Dutch population (72), and has acceptable levels of content validity (70, 73).

Healthcare costs will be measured using the Treatment Inventory of Costs in Patients with psychiatric disorders (TiC-P) Midi (74), a self-report instrument consisting of 8 items. The TiC-P will be administered at each assessment and captures costs related to both intervention costs and use of health care services. These costs cover outpatient services, including therapy costs for both treatment as usual (TAU, i.e., FACT) and AMBIT programs, medical specialist and paramedic visits, home care assistance, and medication.

##### State resilience and trait resilience following childhood trauma

2.3.2.9

Psychosocial resilience refers to an individual’s ability to adapt, recover, and maintain well-being in the face of stress, adversity, or challenges in their social and psychological environment (75, 76). Levels of resilience vary across individuals depending on the presence and interaction of protective psychological, emotional, and social factors. These protective factors are considered to facilitate coping with stressors, thereby reducing the risk of developing mental health problems (76). Resilience can best be understood and measured as a dynamic process of adaptation and recovery during and following stressors (75, 77).

Resilience during a stressor, i.e. state resilience, can be measured as daily life psychosocial resilience in response to momentary stressors. The use of momentary assessments offers a more dynamic, real-time perspective on how people cope with stress in their daily lives. Daily life state psychosocial resilience is assessed using an electronic diary through the Experience Sampling Method (ESM) via the PsyMate smartphone app (78, 79). Participants will complete brief questionnaires 10 times per day over 5 consecutive days. Items assess activity-related stress (“*I find the activity I am currently doing difficult*”) and event-related stress (“*I just experienced a difficult event*”), as well as social context (alone or with others), social stress (e.g., “*I would rather be alone*”), social support (e.g., “*I like the present company”)*, and emotional state (positive and negative). Negative emotions are calculated as the average of responses to feelings such as “*anxious*,” “*lonely*,” “*insecure*,” “*irritated*,” “*down*,” “*guilty*,” and “*gloomy*”, whereas positive emotions are calculated from “*happy*,” “*satisfied*,” “*cheerful*,” “*relaxed*,” and “*enthusiastic*”. All items are rated on a 7-point Likert scale ranging from 1 (*not at all*) to 7 (*very much*). Daily life psychosocial resilience is conceptualized as a decrease in negative emotions and an increase in positive emotions in response to activity-, event- or social-related stress.

Resilience following stressors, such as childhood trauma, provides a broader assessment of an individual’s current mental health and well-being in the aftermath of early adverse experiences. Trait psychosocial resilience is quantified using the residual variance method (80–82), a statistical approach that operationalizes resilience as the extent to which an individual functions better (or worse) than expected given their level of experienced stress or adversity. Specifically, resilience is calculated as the individual residual variance from the population average, based on a regression of current mental health functioning on childhood experiences. This method provides an objective, quantitative measure of resilience and allows examination of how both intrinsic and external factors contribute to an individual’s capacity to cope with stressors. Trait resilience is assessed using a combination of mental wellbeing instruments (e.g., GAF, AIM, C-SSRS) and self-reported childhood adverse events (e.g., CTQ, YCAS) (80–82).

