### Secondary analyses

3.2

As for the primary analysis multilevel (mixed) models will be used for evaluation of the course of the ESM outcome variables over time. Since ESM data of each questionnaire is nested within days and again within the measurement period (T0, T1 or T2), measurements cannot be deemed independent, which requires the analysis of the data within a multilevel structure. The different levels for the multilevel (mixed) model analysis will be: 1) participant, 2) measurement wave, 3) outcome measure, and 4) location of sampling.

In order to compare within group differences (AMBIT informed-MBT vs AMBIT-PD) in the AMBIT condition on the primary outcome, multilevel (mixed) model analyses will be conducted to, with baseline scores (T0), scores after 9 months (T1), and at the end of treatment after 18 months (T2) as dependent variables and treatment (AMBIT informed-MBT and AMBIT-PD) as independent variable.

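### State resilience from the diary is worded at odds with its own concept, and the stated ESM model has no stress term and no day level, so as written it does not target a response to momentary stress

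*Protocol article*

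**What the plan says.** Section 2.3.2.9 opens with a general concept. Resilience is a person's "ability to adapt, recover, and maintain well-being in the face of stress, adversity, or challenges", and "Resilience can best be understood and measured as a dynamic process of adaptation and recovery during and following stressors". State resilience is the part that "can be measured as daily life psychosocial resilience in response to momentary stressors". The diary supplies the data: "Participants will complete brief questionnaires 10 times per day over 5 consecutive days". Activity, event and social stress are rated at the prompts, as are the negative and positive emotions, all on scales from 1 to 7. The section then says that daily-life resilience is "a decrease in negative emotions and an increase in positive emotions in response to activity-, event- or social-related stress". The only composites it defines are the average of the negative items and the average of the positive items.

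Section 3.2 gives the analysis: "multilevel (mixed) models will be used for evaluation of the course of the ESM outcome variables over time". It justifies a multilevel structure as follows: "Since ESM data of each questionnaire is nested within days and again within the measurement period". The levels it then lists are participant, measurement wave, outcome measure and sampling location. Section 3.1.3 gives the same list for the OQ-45.2, which is filled in once per wave.

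**The concern.** There are three separate difficulties.

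- **Definition.** Taken at its word, the sentence describes someone whose mood gets better when stress occurs. A patient whose mood holds steady under stress has maintained well-being, yet does not fit the sentence.
- **Model.** A response to stress is a within-person relation between the stress rating and affect across prompts. The stated model follows the diary variables over time and names no stress predictor or stress interaction. Applied to the two composites that the article defines, it would describe mood level.
- **Levels.** The list has no place for days or prompts, although the sentence before it gives nesting within days as a reason for the multilevel structure.

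The diary is the heaviest demand on participants. From Table 1, 2 minutes × 10 prompts × 5 days = 100 minutes per wave, or 300 minutes over three waves. All other timed participant instruments at T0 add up to 92 to 97 minutes. If a course of mean affect were read as resilience, fewer stressors or a lighter mood could pass for better coping, and a real fall in reactivity could go unseen.

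**Working it through.** The plan gives no figure to reproduce here. The check compares the texts, then shows by example whether the two quantities can differ.

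**Texts side by side**

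1. Concept (2.3.2.9): adapt, recover, maintain. An unchanged mood under stress satisfies it.
2. Working definition (2.3.2.9): negative emotions go down and positive emotions go up in response to stress. An unchanged mood does not satisfy it literally.
3. Model (3.2): diary variables over time. No stress term, stress-by-wave-by-condition term or lag is named. The article does not say what the ESM outcome variables are, and it defines no derived stress-response score.
4. Levels (3.2): the stated nesting is prompts in days in measurement periods. The list includes wave and participant but neither day nor prompt.

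**Hand example (all values assumed)**

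Let mean negative affect = level + reactivity × mean stress, with stress counted from the scale floor.

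- Reactivity stays at 0.30 and mean stress falls by 0.5: change = 0.30 × 0.5 = 0.15 points down.
- Reactivity falls from 0.30 to 0.20, mean stress stays 1.5 above the floor, and affect at the floor is unchanged: change = (0.30 − 0.20) × 1.5 = 0.15 points down.

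The mean falls by the same amount, but only in the second case has the response to stress changed.

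**Simulation (all values assumed, one run per scenario)**

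From the protocol: 160 participants, 3 waves, 10 × 5 = 50 prompts per wave. Assumed: stress SD 1.2 on the 1 to 7 scale, person SD 0.7, residual SD 0.8, every prompt answered, one group only. Negative affect = a + person effect + b × stress + residual. Two mixed models with a random participant intercept were fitted: affect on wave (course only), and affect on wave × stress, with stress centred within person and wave.

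| Scenario | Expected mean affect at T0, T1, T2 (a + b × mean stress) | Course-only slope per wave | Change in reactivity per wave (SE) |
|---|---|---|---|
| A. Fewer stressors, b = 0.30 throughout | 1.5 + 0.30 × 4 = 2.70; 1.5 + 0.30 × 3.5 = 2.55; 1.5 + 0.30 × 3 = 2.40 | −0.147 | −0.001 (0.005) |
| B. b falls 0.30, 0.225, 0.15; mean affect held | 1.2 + 1.2 = 2.40; 1.5 + 0.9 = 2.40; 1.8 + 0.6 = 2.40 | 0.006 | −0.075 (0.005) |
| C. Lower mood level only, b = 0.30 throughout | 1.5 + 1.2 = 2.70; 1.3 + 1.2 = 2.50; 1.1 + 1.2 = 2.30 | −0.203 | 0.008 (0.005) |

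The course-only model reports improvement in A and C, where reactivity is constant, and nothing in B, where it halves. The stress-by-wave term gives the right reading in all three. The standard errors are too small to use for planning, because the simulation has no treatment arms, random stress slopes, day effects or missed prompts.

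**The case against.** A reader might infer that the definition runs in the wrong direction. The text does not support that. The sentence is a conceptual gloss without a score or cut-off. On a continuous slope of negative affect on stress, a lower slope still counts as more resilient, so a calm patient ranks above a reactive one, as under the proposed wording. The sentence could also mean recovery after a stressor, or a smaller response by T2. Both readings are strained, because the section ties state resilience to the time during a stressor and deals with the aftermath under trait resilience. They cannot be excluded, though. For the same reason, the share of patients who could meet the definition should not be estimated: that presupposes a yes/no criterion that the article does not contain.

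A reader might also infer that stress resilience will never be estimated. That goes too far as well. The ESM outcome variables are undefined and could include a reactivity measure, the stress items are collected, and an article may leave the full fixed-effects specification to an analysis plan. Nowhere does the article say that a fall in mean negative affect will be reported as resilience. The examples above show that the two quantities differ, not that the study will substitute one for the other.

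What survives does not rest on silence. The definition and the concept stand in one section and disagree when read literally. The model that is stated does not match the construct. The level list contradicts the sentence before it.

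**Conclusion.** The point holds in a limited form. The wording of state resilience does not fit the section's own concept and needs to be made exact. The ESM model, as stated, does not target a response to momentary stress. Its level list omits the day and prompt levels that its own justification calls for.

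No size can be derived from the documents. Under the assumed values, the course-only slope was −0.147 per wave with unchanged reactivity and 0.006 with halved reactivity, so a course of mean affect is uninformative about resilience in either direction. That conclusion depends on the ESM outcome variables being the mean-affect composites, the only ones the article defines.

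The correction should be made, but its reach is modest: this is one secondary outcome among many, and the primary OQ-45.2 comparison is not affected.

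**What to change.** In section 2.3.2.9, define state resilience as a smaller rise in negative affect and a smaller fall in positive affect per unit of momentary stress. If recovery after the stressor is meant, say so and define it separately.

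In section 3.2:

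- Model prompt-level negative and positive affect on stress centred within person and wave, together with wave, condition and their interactions. Add the participant's mean stress in each wave as a separate covariate, so that exposure and reactivity are kept apart.
- Include a random stress slope, with prompts nested in days, days in waves and waves in participants, in place of the list carried over from the OQ-45.2 model.
- Name stress × wave × condition as the test of state resilience.
- Report mean affect over time as mood, not as resilience.

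The cost is wording and analysis syntax. The stress and emotion items are already collected, so nothing is added for participants. The drawback is that the interaction will be estimated less precisely than a difference in mean affect.

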##### Keyworker/Case manager work satisfaction

2.3.2.10

The Burnout Assessment Tool (BAT) (83) is a 23-item self-report questionnaire to measure burn-out. It includes four dimensions: 1) exhaustion (EX; 8 items), 2) mental distance (MD; 5 items), 3) cognitive impairment (CI; 5 items) and 4) emotional impairment (EI; 5 items). The items are rated on a 5-point Likert scale, ranging from 1 (*never*) to 5 (*always*), with higher scores indicating higher levels of burnout. The Dutch version of the BAT has sound psychometric properties (83, 84).

##### Qualitative interview: the significance of treatment

2.3.2.11

At the end of the study (T2), a qualitative interview will be conducted with 20 participants to determine what patients themselves found to be most conducive or detrimental to their personal recovery in their respective treatment approaches. A qualitative approach was chosen for this study to “enter into the world of participants, to see the world from their perspective, and in doing so make discoveries” (78). To explore the significance of either FACT or AMBIT treatments in the recovery of patients, in-depth semi-structured interviews will be conducted based on grounded theory. All interviews will be transcribed verbatim. The transcripts will be analysed using the qualitative data analysis program ATLAS.TI (Version 24, VERBI Software, 2022), following a grounded theory approach. In the “open coding” phase, interview data will be broken down into smaller components, “codes,” which are specific concepts or themes identified in the data. As data is coded, the researchers continuously compare new data with previous codes and categories. After open coding, related codes are grouped into broader categories. Axial coding is the process of identifying relationships between these categories, which helps in understanding the structure of the emerging theory. As the analysis progresses, the researcher focuses on a core category that seems central to the data. This core category will become the foundation of the emerging theory. Selective coding involves refining and integrating categories around this core category to form a cohesive theory. Researchers will continue to collect data until “theoretical saturation” is reached—when no new information or insights are being discovered, and the categories are well-developed. Sampling decisions are guided by the emerging theory rather than by a predetermined plan. Throughout the process, researchers will write memos to capture their thoughts, hypotheses, and reflections on the data and emerging theory. Memos are a crucial tool for developing the theoretical framework. Theory Development: The final theory is grounded in the data, meaning it is directly derived from the participants’ experiences and the researcher’s analysis.

